## Abstract

**Background:**

Levodopa remains the most effective symptomatic treatment for Parkinson’s disease (PD) more than 50 years after its clinical introduction. However, the onset of motor complications can limit pharmacological intervention with levodopa, which can be a challenge when treating PD patients. Clinical data suggest using the lowest possible levodopa dose to balance the risk/benefit. Istradefylline, an adenosine A_2A_ receptor antagonist indicated as an adjunctive treatment to levodopa-containing preparations in PD patients experiencing wearing off, is currently available in Japan and the US. Preclinical and preliminary clinical data suggested that adjunctive istradefylline may provide sustained antiparkinsonian benefits without a levodopa dose increase; however, available data on the impact of istradefylline on levodopa dose titration are limited. The ISTRA ADJUST PD study will evaluate the effect of adjunctive istradefylline on levodopa dosage titration in PD patients.

**Methods:**

This 37-week, multicenter, randomized, open-label, parallel-group controlled study in PD patients aged 30–84 years who are experiencing the wearing-off phenomenon despite receiving levodopa-containing medications ≥ 3 times daily (daily dose 300–400 mg) began in February 2019 and will continue until February 2022. Enrollment is planned to attain 100 evaluable patients for the efficacy analyses. Patients will receive adjunctive istradefylline (20 mg/day, increasing to 40 mg/day) or the control in a 1:1 ratio, stratified by age, levodopa equivalent dose, and presence/absence of dyskinesia. During the study, the levodopa dose will be increased according to symptom severity. The primary study endpoint is the comparison of the cumulative additional dose of levodopa-containing medications during the treatment period between the adjunctive istradefylline and control groups. Secondary endpoints include changes in efficacy rating scales and safety outcomes.

**Discussion:**

This study aims to clarify whether adjunctive istradefylline can reduce the cumulative additional dose of levodopa-containing medications in PD patients experiencing the wearing-off phenomenon, and lower the risk of levodopa-associated complications. It is anticipated that data from ISTRA ADJUST PD will help inform future clinical decision-making for patients with PD in the real-world setting.

**Trial registration:**

Japan Registry of Clinical Trials, jRCTs031180248; registered 12 March 2019.

## Background

Parkinson’s disease (PD) is a progressive neurodegenerative movement disorder. The mechanism of pathogenesis stems from the striatal deficiency of the neurotransmitter dopamine due to the degeneration of dopaminergic neurons in the substantia nigra pars compacta of the midbrain [1, 2]. The well-recognized clinical manifestations of PD commonly include tremor, rigidity, bradykinesia, akinesia, and postural instability [3].

Levodopa was introduced in the late 1960s for the treatment of PD [4]. Levodopa crosses the blood–brain barrier and is converted to dopamine, and is currently the most effective treatment and an essential drug throughout the clinical course of the disease [5]. However, motor complications, such as the wearing-off phenomenon and levodopa-induced dyskinesia, can be a challenge when treating PD patients with dopaminergic agents over extended durations, with up to 50% of patients developing complications within 5 years of starting treatment [6–9]. Studies have suggested that these complications may be related to the daily levodopa dosage [10, 11]. In order to constrain the need for levodopa dose increases, alternative or adjunctive treatments may be considered. Dopamine agonists are often added to treatment regimens [7, 12] but also have problematic side effects, such as impulse control disorders, sleepiness, and hallucinations [13] which must be considered. Moreover, since levodopa-sparing therapies such as dopamine agonists appear to be less effective than levodopa over time [14], there remains situations in which increasing the levodopa dose is the best option for patients. Thus, the current clinical recommendation is that the lowest possible levodopa dose should be used to balance the risk/benefit profile of treatment [10, 15]. However, adjusting the dose of levodopa must be done cautiously, to avoid causing adverse effects whilst attempting to control symptoms. Over time, it becomes difficult to adjust the dose of levodopa for symptom control without introducing adverse effects, particularly after the onset of the wearing-off phenomenon. Although deep brain stimulation and levodopa-carbidopa intestinal gel are known to be effective for treating the wearing-off phenomenon, they are recommended for patients with late-stage PD due to the need for surgical intervention with these treatments. No current adjunctive pharmacotherapy to enable levodopa dose adjustment has proven sufficient to achieve satisfactory clinical control for many early-stage patients after the onset of the wearing-off phenomenon [16].

The adenosine A_2A_ receptor has been identified as one possible non-dopaminergic target for novel PD drugs. This receptor is highly expressed in the striatum and in the external globus pallidus, particularly in striatopallidal medium spiny neurons which form the indirect pathway in the basal ganglia system that are important for the control of voluntary movement [17]. The adenosine A_2A_ receptor antagonist istradefylline suppresses the excessive activation of the striatopallidal medium spiny neurons that occurs in PD, normalizing basal ganglia function, and thus improving PD symptoms [18, 19]. The results from several double-blind trials [20–24], meta-analyses [25–27], and a post-marketing surveillance study [28] have shown that istradefylline improves OFF time in the treatment of advanced PD. Istradefylline is currently available in Japan and the United States and is indicated as an adjunctive treatment to the levodopa-containing preparations in PD patients experiencing the wearing-off phenomenon [29].

Preclinical and clinical studies have suggested that adjunctive istradefylline may provide sustained antiparkinsonian benefits without a levodopa dose increase [30–32]. In primate studies, administration of istradefylline in conjunction with low-dose levodopa or with threshold-dose levodopa plus threshold-dose dopamine agonists was found to significantly improve motor function [31, 33]. A small-scale (*n* = 15), double-blind, placebo-controlled study conducted in the United States reported that adjunctive istradefylline (40 mg/day) administered with threshold-dose levodopa significantly improved motor function (measured using the Unified Parkinson’s Disease Rating Scale [UPDRS] part III score) [30]. In Japan, a small (*n* = 15) retrospective clinical study demonstrated that istradefylline might enhance the effects of low-dose levodopa and improve motor symptoms [32]. Furthermore, data from an interim analysis of a post-marketing surveillance study showed that in the real-world setting, where physicians are able to optimize treatment at their discretion, the dosage of levodopa in patients receiving istradefylline did not change significantly over a one-year period [28]. However, robust clinical data from large, well-designed prospective trials on the effect of istradefylline on levodopa sparing are lacking. Therefore, the objective of this multicenter, randomized, open-label, parallel-group controlled study (ISTRA ADJUST PD) is to evaluate the effect of adjunctive istradefylline on the cumulative dose of levodopa-containing products in patients with PD. This design was determined by the fact that simply reducing the levodopa dosage to directly evaluate levodopa-sparing effects is not ethically feasible. This assessment of whether istradefylline can suppress levodopa dose increases will provide indirect evidence for its putative levodopa-sparing effect. The efficacy and safety of istradefylline will also be evaluated. In this report, we describe the protocol and design rationale of the ISTRA ADJUST PD study.

## Methods/Design

### Patients

Patients eligible for inclusion in the ISTRA ADJUST PD study will be those with PD who meet all of the inclusion criteria and do not meet any of the exclusion criteria. Inclusion criteria include taking levodopa-containing medications ≥ 3 times daily with a daily dose of 300–400 mg; experiencing wearing-off phenomenon; age 30–84 years; PD diagnosed according to The International Parkinson and Movement Disorder Society (MDS) criteria [34]; modified Hoehn & Yahr (mH&Y) scale [35] (ON) stage ≤ 3; and provided written informed consent. Patients concomitantly taking anti-PD drugs other than levodopa, such as dopamine agonists, catechol-o-methyl-transferase inhibitors, and monoamine oxidase type B inhibitors, will also be eligible for inclusion. Exclusion criteria include previous treatment with istradefylline; receipt of any investigational drug within 4 months before the date of enrolment; presence of dementia or a Japanese version of the Mini-Mental State Examination (MMSE) score of ≤ 23; prior neurosurgery for PD (e.g., stereotactic surgery, deep brain stimulation, gamma knife); current or planned treatment with levodopa/carbidopa hydrate enteral suspension; moderate or severe hepatic disorder; PD treatment initiation or regimen change within 4 weeks before enrolment; receipt of strong CYP3A4 inhibitors (e.g., itraconazole, clarithromycin) within 14 days before enrolment; lactation or pregnancy; and any other reason for ineligibility according to the discretion of the investigator.

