### Study design, treatments, and blinding

The ISTRA ADJUST PD study is a multicenter, randomized, open-label, parallel-group controlled study (Fig. 1). Study participants will be randomly assigned to either the istradefylline group or the control group in a 1:1 ratio. Randomization will be centrally performed via computer allocation, using a minimization method and stratified according to age (< 60 or ≥ 60 years), levodopa equivalent dose (< 400 or ≥ 400 mg/day), and dyskinesia (presence or absence). The study will be conducted from February 2019 to February 2022 (with the registration period lasting until November 2020), and the expected duration of involvement for each participant is 37 weeks. The observation schedule is shown in Table 1; most observations will be conducted at 4- or 12-weekly intervals during the study period.

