**Fig. 1 Fig1:**
[figure not shown]
ISTRA ADJUST PD study design. W, week

**Table 1 Tab1:** Observation schedule

	Date of consent or enrollment	Observation period (week)											
		0	1^a^	4	8	12	16	20	24	28	32	36^b^	37^c^
Informed consent	●												
Eligibility confirmation	●	●											
MMSE	●												
Patient background	●												
Medical history/complications		●											
Decision on dose increase of levodopa-containing medications				●	●	●	●	●	●	●	●	●	
CGI-S		●		●	●	●	●	●	●	●	●	●	
CGI-I				●	●	●	●	●	●	●	●	●	
PGI-S		●		●	●	●	●	●	●	●	●	●	
PGI-I				●	●	●	●	●	●	●	●	●	
mH&Y (ON/OFF)		●				●			●			●	
MDS-UPDRS (part I, II, III, IV)		●				●			●			●	
PDQ-39		●				●			●			●	
Wearable device data	●					●			●			●^e^	
Symptom diary^d^	●					●			●			●^e^	
Hospitalizations	●	●	●	●	●	●	●	●	●	●	●	●	●
Concomitant medication check	●	●	●	●	●	●	●	●	●	●	●	●	●
Adverse events	●	●	●	●	●	●	●	●	●	●	●	●	●
Information on discontinuation		At any time											
Data entry into the case report form		Within 2 weeks after each visit											

*CGI-I* clinical global impressions of improvement, *CGI-S* clinical global impressions of severity, *MDS-UPDRS* Movement Disorder Society Unified Parkinson’s Disease Rating Scale, *mH&Y* modified Hoehn & Yahr scale, *MMSE* Mini-Mental State Examination, *PDQ* Parkinson’s disease questionnaire, *PGI-I *patient global impressions of improvement, *PGI-S* patient global impressions of severity

^a^Istradefylline group only

^b^Or the day immediately after discontinuation

^c^Not a mandated visit if judged to be unnecessary

^d^Symptoms will be recorded in symptom diaries by study participants or their family members/caregivers. The investigator, subinvestigator, or study cooperator are also allowed to record symptoms in the diary during the visit, or in the case that the patients are hospitalized. Visits will be conducted in an outpatient setting; however, inpatient visits will also be allowed if needed

^e^Wearable devices will be worn for one additional week after the end of the observation period (from Week 36), and symptoms are also recorded in the diary during this period; if the patient has discontinued, these recordings are terminated on the day of discontinuation

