The criteria for the titration of levodopa-containing medications are as follows: if the clinical global impression of severity scale (CGI-S) is ≥ 4 on the day of observation, the dose is incrementally increased by 50 mg/day. If an intolerable adverse reaction occurs due to the dose increase, reduction of the dose of the levodopa-containing medication is allowed (at the physician’s discretion; no reduction amount is specified). For levodopa, only a dose increase of 50 mg/day per visit will be allowed.

Once-daily oral administration of a 20 mg istradefylline tablet will be started at Week 0. At Week 1, if the treatment is well tolerated and motor symptoms persist, the dosage of istradefylline will be increased to 40 mg, once daily. Dose reduction is allowed if treatment is not tolerable.

Changes in the dosage and dosing regimen of anti-PD drugs are not permitted within 4 weeks before enrollment and during the treatment period. However, dose reduction of a specific drug is permitted, if intolerable adverse reactions causally associated with that drug appear.

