### Statistical methods

There have been no previous studies investigating the effect of istradefylline treatment on the flexibility of the doses of levodopa-containing formulations. Thus, we used real-world data based on information from the medical claims database (Medical Data Vision Co., Ltd., Tokyo, Japan) to estimate the between-group difference in the Mann–Whitney U test by simulating cumulative L-DOPA doses in PD patients (non-istradefylline treatment), which would ensure a power of 80% with groups of 50 patients. In this condition, an approximate 21.3% in between-group difference over a period of 9 months (270 days) is detectable as the area under the curve (AUC) of cumulative additional L-DOPA doses between treatments (data on file; Kyowa Kirin Co., Ltd., Tokyo, Japan). Based on the mean additional levodopa dose over 9 months (approximately 265 mg) in a previously published study [36], recommendation from the Expert Medical Advisory board for this study, and the clinical experience in Japan, we anticipated that istradefylline might suppress the dose increase of levodopa-containing medications by 20%. Therefore, the sample size was set at 111 patients, to allow for 10% drop-outs and to ensure that there were 50 patients per group with data evaluable for the efficacy analyses.

The efficacy and safety analysis sets will include all patients who meet the inclusion criteria and do not meet the exclusion criteria, with the exception of those who withdraw consent before the start of the observation period (Week 0) or are withdrawn by the study investigator, and those randomly assigned to istradefylline treatment but who do not start administration of istradefylline. The patient background data that will be collected will include date of birth (if not disclosed, age at the date of consent), sex, height, weight, caregiver availability, pregnancy, hospitalization, year of onset of PD, year of onset of wearing-off, family history of PD, year of initial treatment with levodopa, daily dose and number of administrations of levodopa, levodopa equivalent dose, MMSE score, and mH&Y (ON/OFF).

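### The efficacy set is defined by exclusion criteria that end in an open-ended investigator judgement, so a subjective eligibility decision can remove a randomised patient from the primary comparison

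*Protocol article*

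**What the plan says.** - **Entry criteria (Patients).** After a series of mostly checkable exclusions (earlier istradefylline, MMSE of 23 or less, prior neurosurgery for PD, recent strong CYP3A4 inhibitors), the list ends with "any other reason for ineligibility according to the discretion of the investigator".
- **Analysis sets (Statistical methods).** "The efficacy and safety analysis sets will include all patients who meet the inclusion criteria and do not meet the exclusion criteria". Exceptions follow for patients who withdraw consent before Week 0 "or are withdrawn by the study investigator, and those randomly assigned to istradefylline treatment but who do not start administration of istradefylline".
- **Design (Study design, treatments, and blinding).** "The ISTRA ADJUST PD study is a multicenter, randomized, open-label, parallel-group controlled study", with patients "randomly assigned to either the istradefylline group or the control group in a 1:1 ratio".
- **Timing (Table 1).** The row "Eligibility confirmation" is marked at consent or enrolment and at Week 0, and at no later visit. Study drug begins on that same day: "Once-daily oral administration of a 20 mg istradefylline tablet will be started at Week 0".

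**The concern.** A discretionary exclusion is ordinary and harmless at screening, because it acts before allocation and affects both future arms alike. The difficulty comes from using the same list a second time to decide who is analysed. Removing a randomised patient for an entry violation leaves the comparison unbiased when three conditions hold: the breach is objective, it rests on facts that predate randomisation, and it is looked for equally in both arms. The discretionary item fails the first condition by its nature, since it has no content, no date and nothing to audit. The text does not secure the other two.

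At stake is the primary endpoint, the cumulative additional levodopa dose. If patients likely to need more levodopa are judged unsuitable more readily in one arm than in the other, the arms differ before any drug effect. A levodopa-sparing result could then be created or hidden.

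**Working it through.** **Reading the sections together.**
1. The efficacy set requires that no exclusion criterion is met (Statistical methods).
2. One of those criteria is the investigator's unrestricted discretion (Patients).
3. The exception for patients assigned to istradefylline who never start would be unnecessary unless the set were drawn from randomised patients. The eligibility condition therefore acts on randomised patients.
4. The trial is open-label, so once allocation has been made the investigator knows it.
5. Neither a cut-off for the eligibility judgement at randomisation nor an all-randomised primary analysis is stated.

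A randomised patient can therefore leave the primary comparison on a subjective judgement. Whether the Week 0 check comes before or after allocation is not stated.

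**The plan's own figure.** For 100 evaluable patients and 10% drop-out, 100 / 0.9 = 111.1. The plan states 111, and 111 × 0.9 = 99.9, so the figure is reproduced to rounding. The claims-database simulation behind the 80% power and the 21.3% detectable difference is data on file and cannot be reproduced. No stated figure changes because of this point.

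**Precision is not the issue.** With 50 per arm and 80% power at two-sided 5%, the standardised difference is (1.960 + 0.842) × √(2/50) = 0.560. At 50 against 45, power is Φ(0.560 / √(1/50 + 1/45) − 1.960) = 77.8%. Losing five patients costs about two points of power. The concern is bias.

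**Size of the bias, by illustration.** The assumptions are the reviewer's, not the documents': no true effect; 55 per arm (111 / 2, rounded down); Mann–Whitney U test at two-sided 5%; 20,000 runs. The *k* patients with the worst baseline prognosis are removed from the istradefylline arm only, and prognosis correlates with outcome at ρ.

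| ρ | *k* | False positive favouring istradefylline | Two-sided error |
|---|---|---|---|
| 0.3 | 0 | 2.6% | 5.0% |
| 0.3 | 2 | 3.4% | 5.4% |
| 0.3 | 5 | 4.4% | 5.6% |
| 0.5 | 0 | 2.5% | 4.9% |
| 0.5 | 2 | 3.9% | 5.5% |
| 0.5 | 5 | 6.2% | 7.1% |

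**A model closer to the trial.** Nine decisions of 50 mg are taken at Weeks 4 to 36 and carried to Week 37 (day 259). The largest possible cumulative addition is 50 × (9 × 259 − 28 × 45) = 50 × 1,071 = 53,550 mg. Three assumed severity mixes were used, with 4,000 runs each. Removing 3 or 5 istradefylline patients with high, noisily judged baseline severity gave 3.9–5.2% or 5.2–6.7% in one run. A second run, which removed the highest-ranked patients and set the noise SD equal to the between-patient SD, gave 4.8–5.8% or 6.7–7.5%. Without exclusions the rate was 2.1–2.8%.

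**The case against.** The strongest reply is that these are entry criteria. Table 1 places the last eligibility check at Week 0 and nothing says eligibility is judged again later. If allocation follows that check, the scheduled judgement is made without knowledge of the arm. Five discretionary removals from one arm would also be nearly half of the whole drop-out allowance (10% of 111, about 11 patients), and the documents suggest no such number. An analysis plan is promised before database lock and may tighten the rule.

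Much of this stands, and it limits the point. Three stronger readings are tempting, and the documents do not support them:

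- **A patient is followed to Week 37 and then dropped as unsuitable.** No section describes an eligibility judgement after Week 0.
- **Scrutiny of eligibility is unequal because only the istradefylline arm has a Week 1 contact.** That contact follows the last eligibility check, and Table 1 marks it for hospitalisations, concomitant medication and adverse events only.
- **Error rates reach 5% or 8–9%.** Those values come from removing 3 or 5 patients from the top third of the cumulative levodopa dose. Dose decisions begin at Week 4, so that outcome does not exist at the last scheduled check.

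What does not stand is the view that this is merely detail left to the analysis plan. The article states an analysis-set rule, and an analysis plan faithful to it would inherit the problem. Who reviews eligibility listings, and whether exclusions are tabulated by arm, are properly matters for that plan and are not criticised here.

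**Conclusion.** The point holds as a defect in a stated rule: the efficacy set depends on a criterion that is not objective and is not tied to data from before randomisation, in an open-label trial. It shows that a randomised patient can be removed on judgement. It does not show that this will happen, or that the judgement would be made with the arm known.

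The illustrated effect is modest: from about 2.5% to roughly 3.4–6% for false positives favouring istradefylline, and about 7% under stronger assumptions. This rests on 2 to 5 removals, all from one arm and all in the favourable direction, with baseline prognosis moderately related to outcome. The documents supply neither the count nor the correlation, and the bias could run the other way.

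Two other clauses in the same sentence lead to the same bias more directly. One is withdrawal by the investigator, where it is unclear whether the Week 0 limit applies. The other is the removal of non-starters from the istradefylline arm, which has no counterpart among controls.

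**What to change.** In Statistical methods, define the primary efficacy set as all randomised patients, analysed in the arm to which they were assigned. Allow removal for ineligibility only where an objective criterion was breached on data dated before randomisation (for example prior istradefylline, MMSE of 23 or less, or prior neurosurgery), and never under the discretionary criterion. Keep the eligibility-restricted set as a sensitivity analysis. The same wording should replace the investigator-withdrawal clause and the one-arm exclusion of non-starters for the primary analysis. The discretionary item can stay in the entry criteria as a screening rule.

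The cost is one sentence. A few patients whom the investigator thought unsuitable, or who never started study drug, stay in the comparison and may dilute the effect slightly. Visits, treatment and sample size are unchanged.
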